# Effectiveness, safety and cost-effectiveness of vaporized nicotine products versus nicotine replacement therapy for tobacco smoking cessation in a low-socioeconomic status Australian population: a study protocol for a randomized controlled trial

**DOI:** 10.1186/s13063-022-06644-8

**Published:** 2022-09-14

**Keywords:** Cost-effectiveness, Electronic cigarettes, Randomized controlled trial, Smoking cessation, Social disadvantage, Tobacco

## Abstract

**Background:**

In Australia, tobacco smoking rates have declined but inequalities remain with significantly higher smoking prevalence among low-socioeconomic populations. Clinical trial data suggest vaporized nicotine products (VNPs) aid smoking cessation. Most VNP trials have used refillable tank systems, but newer generation (pod) devices now comprise the largest market share yet have limited clinical trial evidence on safety and effectiveness. This study evaluates the effectiveness, safety and cost-effectiveness of VNPs (pod and tank device) compared with nicotine replacement therapy ([NRT]—gum or lozenge) for smoking cessation.

**Methods:**

This is a two-arm, open-label, superiority, parallel group, randomized controlled trial (RCT) with allocation concealment and blinded outcome assessment. The RCT is conducted at the National Drug and Alcohol Research Centre at the University of New South Wales, Sydney, Australia. Participants are people who smoke daily, are interested in quitting and receive a government pension or allowance (*N* = 1058). Participants will be randomized (1:1 ratio) to receive 8 weeks of free: VNPs, with pod (40 mg/mL nicotine salt) and tank device (18 mg/mL freebase nicotine) in mixed flavours; or NRT (gum or lozenge; 4 mg). All participants will receive daily text message behavioural support for 5 weeks. Assessments will be undertaken by telephone at baseline, with three follow-up calls (two check-in calls within the first month and final follow-up at 7 months post randomization) to ascertain smoking status, treatment adherence and adverse events. The primary outcome is 6-month continuous abstinence verified by carbon monoxide breath test of ≤5ppm at 7-month follow-up. Safety and cost-effectiveness of VNPs versus NRT will also be evaluated.

**Discussion:**

Further data are required to strengthen certainty of evidence for VNPs aiding smoking cessation, particularly for newer generation pod devices. To our knowledge, this trial is the first to offer choice of VNPs and no comparative effectiveness trial data exists for new pod devices. If effective, the findings can inform wider implementation of VNPs to aid smoking cessation in a priority group.

**Trial registration:**

Australian New Zealand Clinical Trials Registry ACTRN12621000076875. Registered on 29 January 2021. https://www.anzctr.org.au

**Supplementary Information:**

The online version contains supplementary material available at 10.1186/s13063-022-06644-8.

## Background

In Australia, 10.7% of Australians (aged 18 or older) smoke daily (approximately 2.1 million people) [1]. Smoking rates are higher among low-socioeconomic (low-SES) groups in Australia and globally [1–3]. A recent (2020–2021) national survey of Australians reported that persons from disadvantaged areas were *more than three times as likely* to be current daily smokers than those from most advantaged areas, 17.8% vs. 5.8%, highlighting this important driver of health inequalities [1]. Low-SES smokers face multiple barriers to smoking cessation including financial stress, high smoking rates in their social network and higher nicotine dependence [4, 5]. Despite public health efforts, there is a lack of evidence on effective smoking cessation interventions for low-SES groups [6].

In most countries, the use of vaporized nicotine products (VNPs), commonly referred to as electronic cigarettes or vaping, has increased over the last decade. Recent (2019) Australian National Drug Strategy Household Survey found that 39% of adults who smoke had ever used a VNP, compared with 31% in 2016 [3]. Furthermore, 32% of people who use VNPs report using them to quit smoking, 22% to reduce the number of cigarettes smoked and 17.8% to stop them going back to smoking regular cigarettes [3]. A national survey in the United Kingdom (UK) found 33% of smokers report using VNPs for smoking cessation, compared with 22% who report using nicotine replacement therapy (NRT) [7].

VNPs have the potential to be more effective than NRT because of their superior nicotine delivery [8–13], a greater reduction in reported urges to smoke [10, 14] and greater sensorimotor replacement, and they appear to have greater adherence than NRT [10, 11, 15]. Furthermore, VNPs are generally cheaper than cigarettes and so are considered more affordable for low-income populations. In recent years, newer fourth-generation pod VNP devices have emerged, which appear to have improved pharmacokinetic data compared to early-generation devices [11, 16, 17]. Fourth-generation VNPs can produce concentrations of nicotine comparable to NRT [8], with faster nicotine delivery and a pharmacokinetic profile similar to smoking [12, 13, 18, 19]. Regarding safety, clinical trial data on VNPs report a range of relatively minor short-term side effects such as headache, dry mouth, cough, nausea and mouth and throat irritation [20]. Whilst VNPs are generally considered much less harmful than cigarette smoking because they expose users to fewer harmful and potentially harmful chemicals [9], data on adverse effects associated with long-term VNP use are required.

Clinical trial evidence for VNPs aiding smoking cessation is limited by the number and quality of trials. A 2021 Cochrane review of 61 studies, including 34 randomized controlled trials (RCTs) [20], found moderate-certainty evidence (4 studies, 1924 participants) that VNPs were more effective than NRT for long-term cessation rates (risk ratio (RR) 1.53, 95% confidence interval (CI) 1.21 to 2.93; *I*^2^ = 0%). A longstanding limitation of these trials, documented within this review, is that most RCTs are small-scale RCTs, and some of the larger trials were underpowered to detect statistically significant differences between VNPs and comparators [20]. Limitations of previous trials include poor nicotine delivery or low concentrations of nicotine in early-generation VNPs and poor to modest retention of participants at final follow-up [20]. To our knowledge, there is no existing comparative effectiveness clinical trial data on fourth-generation pod VNPs for smoking cessation.

Given Australia currently bans the sale of nicotine liquids for vaping without a prescription, whereas these products are far more accessible in the UK, United States (US) and New Zealand, there is a need for more Australian data comparing VNPs with standard smoking cessation medications, such as NRT. The main objective of this trial is to evaluate the effectiveness, cost-effectiveness and safety of VNPs compared with oral NRT. Given the significantly higher smoking rates among low-SES populations, this trial specifically evaluates the comparative effectiveness of VNPs to NRT in this group. Pragmatic use of nicotine products for smoking cessation involves limited behavioural support and choice from a range of products and flavours. In this trial, to partially mimic real-world settings, we offer participants a choice of VNP or NRT product in each arm respectively and provide minimal behavioural support via text messages [21].

### Aim

To evaluate the effectiveness, safety and cost-effectiveness of VNPs (pod device with 40 mg/mL nicotine salt and tank device with 18 mg/mL freebase nicotine) plus text message behavioural support compared with oral NRT (gum or lozenge; 4 mg) plus text message behavioural support for smoking cessation in Australian low-SES daily smokers who are willing to quit.

### Hypotheses

It is hypothesized (H), compared to comparator group (NRT), the intervention group (VNP) will show at 7-month follow-up:H1 (effectiveness): a significantly higher 6-month biochemically verified continuous abstinence rate;H2: (safety): comparable short-term safety outcomes (demonstrated via proportion of serious adverse events (SAEs) and adverse events (AEs) reported for NRT and VNP arms); andH3 (cost-effectiveness): greater cost-effectiveness in achieving 6-month continuous abstinence.

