## Methods

### Design

This is a parallel two-group, superiority, open-label RCT with a 1:1 treatment allocation ratio. This study is reported using the SPIRIT reporting guidelines [22].

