### Sample size

The study plans to enrol 1058 participants in total (529 per group) to provide a power of 80%, for a two-sided significance level of 0.05 and assuming a 20% loss to follow-up. In Hajek et al. [40], 12-month verified abstinence rates in the NRT group were 9.9%. Assuming ~25% relapse between 6 and 12 months [41], this would translate to a 6-month abstinence rate of 13.2%. However, we expect abstinence rates to be 40% lower in the comparator arm in this trial as we are (a) using lower intensity behavioural support (text messaging compared to multi-session face-to-face), (b) providing a single NRT (the majority of participants in Hajek et al 2019 used combination treatment) and (c) recruiting participants from a population that is expected to have low quit self-efficacy. Using these assumptions, the estimated verified 6-month continuous abstinence rate in our NRT group is 8%. Using the risk ratio of 1.8 found in the Hajek et al. study, we assume a 6-month verified continuous abstinence rate of 14% in our VNP group. In a recent smoking cessation RCT among Australian low-SES smokers (*n* = 1047), 84% retention was achieved at final 8-month follow-up, despite higher study demands on participants (length and number of calls) [42]. Given the current study has fewer study demands on participants and a shorter follow-up period compared to the previous study, we expect the loss to follow-up to be at least comparable.

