#### Treatment effects

A Bayesian beta-binomial posterior distribution for the quit proportions will be constructed for the NRT and VNP group separately and one million random draws from each posterior distribution will be taken. Superiority of VNP over NRT will be established if the posterior probability of quitting in the VNP arm is greater than corresponding posterior probability in the NRT arm in 97.5% of random draws. A beta(1,1) prior (non-informative) will be used for the primary analysis, but sensitivity analyses will use informative beta priors based on previously published results for NRT and VNP. Given the field is evolving rapidly with new studies, it is inappropriate to pre-specify exact priors at this stage. The trial statistical analysis plan will be updated prior to data analysis and the most updated priors will be selected from the latest Cochrane review. A similar Bayesian analysis will be conducted for the proportions of SAEs and AEs in each study arm, and 95% credible intervals will be reported for abstinence rates in each arm and for the difference in quit proportions.

The primary effectiveness analysis will be conducted in accordance with the intention-to-treat principle. All randomized participants will be included in the analysis set and will be classified as still smoking unless self-reported continuous abstinence is verified by CO breath test. The primary analysis will consider individuals with missing smoking status at follow-up as treatment failures. Sensitivity analyses will be conducted with alternative missing data assumptions and excluding participants with protocol deviations [43]. Further details of all statistical analyses will be included in the statistical analysis plan.

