#### Tolerability analysis

The primary AE outcome will be the difference in the rate of AEs between the treatment groups. The incidence of all suspected AEs will be summarized by treatment group, as follows: type, severity, causality, action taken and outcome. All randomized participants who take at least one dose of NRT or VNP will be included in the safety analyses. Comparison of the frequency of treatment withdrawal between the NRT group and VNP group will be tested using chi-square statistics. The number of participants discontinuing treatment prematurely for any reason will be summarized by treatment group and by reasons for discontinuation. The DSMC provide periodic oversight of AE data. For the primary AE outcome, the proportion of reported AEs occurring between treatment initiation and 7-month follow-up will be compared between the two treatment groups. The most frequent AEs (occurrence of ≥5%) will be presented by MedDRA term and compared between treatment groups. All SAEs will be presented by MedDRA term, event type and treatment group. An analysis of AE occurrence between VNP and NRT will also be conducted for participants reporting an AE start date within 28 days after the baseline interview. The between-group difference for the rate of AEs will be modelled using negative binomial regression. The analysis of the AEs will be summarized using the incidence rate ratio and 95% CI for the VNP group compared with the NRT group. This analysis will be two-sided and use a significance threshold of 0.05.

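### H2 predicts comparable safety, but the stated safety analyses look for a difference and the protocol gives no criterion for comparable

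*Protocol article*

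**What the plan says.** Under Hypotheses, H2 predicts that, at 7-month follow-up, the VNP arm will show "comparable short-term safety outcomes (demonstrated via proportion of serious adverse events (SAEs) and adverse events (AEs) reported for NRT and VNP arms". Safety is one of the three components of the Aim, beside effectiveness and cost-effectiveness.

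The inference for safety is stated in two places.

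- **Treatment effects:** "A similar Bayesian analysis will be conducted for the proportions of SAEs and AEs in each study arm". The analysis it resembles is the beta-binomial comparison of quitting. There, superiority is declared if VNP exceeds NRT in 97.5% of posterior draws. The 95% credible intervals in the same sentence are named for abstinence rates and for the difference in quit proportions, not for AEs or SAEs.
- **Tolerability analysis:** the primary AE outcome is a between-group difference in AE rate. It is modelled by negative binomial regression and reported as an incidence rate ratio with a 95% confidence interval. "This analysis will be two-sided and use a significance threshold of 0.05". Treatment withdrawal gets a chi-square test. SAEs are tabulated by group, so their only inferential analysis is the Bayesian one.

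On design, the protocol says: "This is a parallel two-group, superiority, open-label RCT with a 1:1 treatment allocation ratio". The sample size rests on abstinence alone. No margin, safety event rate or other criterion for *comparable* appears.

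**The concern.** H2 asserts similarity and says how it is to be demonstrated. The stated analyses ask whether the arms differ. Failing to find a difference is weak evidence of similarity unless the analysis could have found a difference that matters, and the protocol does not say what size of difference matters.

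The risk runs in an awkward direction. The rarer the event, the less information the trial holds and the more likely a non-significant result, so H2 would look best supported where the data say least. That is the SAE comparison, which readers of a safety claim will care about most.

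**Working it through.** **1. The plan's own figure.** The protocol sizes the trial "to provide a power of 80%, for a two-sided significance level of 0.05 and assuming a 20% loss to follow-up", with 8% abstinence on NRT and 14% on VNP. With unpooled variance:

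n = (1.960 + 0.842)² × (0.08×0.92 + 0.14×0.86) / 0.06² = 7.849 × 0.194 / 0.0036 = 423 per arm.

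423 / 0.8 gives 529 per arm, 1058 in total. This matches exactly. No safety quantity enters it.

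**2. Inputs for H2.** The safety set is all randomized participants who take at least one dose, so at most 529 per arm. The protocol gives no AE or SAE rates, so every rate below is an assumption shown as a range.

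**3. SAE sensitivity at 529 per arm.** Power uses the two-proportion normal approximation, two-sided 0.05, pooled variance under the null. For 2% against 3%:

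- null SE = √(2×0.025×0.975/529) = 0.00960
- alternative SE = √((0.02×0.98 + 0.03×0.97)/529) = 0.00960
- power = Φ((0.010 − 1.96×0.00960)/0.00960) = Φ(−0.92) = 18%

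The upper limit of the risk ratio (RR), when both arms show the same rate p with e = 529p events each, is exp(1.96 × √(2×(1/e − 1/529))).

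| Assumed NRT SAE rate | Power, 1.5-fold | Power, 2-fold | Upper 95% RR limit if observed rates are equal |
|---|---|---|---|
| 1% | 11% | 27% | 3.3 |
| 2% | 18% | 48% | 2.3 |
| 3% | 25% | 65% | 2.0 |
| 5% | 39% | 87% | 1.7 |

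This z-test is not the planned SAE analysis, so the Bayesian rule was simulated as well: beta(1,1) priors, 97.5% threshold, 529 per arm, 3000 trials. It flags 2% against 3% in about 18% of trials, 2% against 4% in about 47%, and 3% against 6% in about 66%. The two approaches agree closely.

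**4. AE proportions at 529 per arm.**

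| Assumed NRT AE proportion | Power, 5 points higher | Power, 10 points higher |
|---|---|---|
| 30% | 41% | 93% |
| 50% | 37% | 91% |
| 70% | 45% | 97% |

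**5. AE rates, negative binomial.** With mean μ events per person on NRT, dispersion k and rate ratio r, SE(log ratio) = √[((1/μ + k) + (1/(μr) + k))/529]. For μ from 0.5 to 2 and k from 0.5 to 2, power is 46% to 96% for a ratio of 1.25 and at least 93% for 1.5. With an observed ratio of 1, the 95% interval runs from 0.79–1.27 at the widest to 0.89–1.13 at the narrowest.

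**6. What a margin would require.** With equal true rates p, one-sided 0.025 and 80% power, n per arm = 7.849 × 2p(1−p)/m² for margin m.

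- SAE, 2-point margin: 389 at p = 1%, 770 at 2%, 1143 at 3%.
- AE at 50%: 393 for a 10-point margin, 1570 for a 5-point margin.

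These margins are illustrations only. With at most 529 per arm, a 10-point AE margin is within reach and a 5-point one is not. A 2-point SAE margin is within reach only if SAEs are near 1%.

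**The case against.** Four points can fairly be made in the protocol's defence.

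- **The planned outputs could support similarity.** The rate ratio comes with a 95% interval, and beta-binomial posteriors give the probability that a difference lies below any chosen margin. This stands: what is missing is the criterion, not the machinery. A reader might infer that the analyses can never inform comparability, and that goes too far.
- **No rule equates a null result with comparability.** A reader might infer that the trial will declare H2 confirmed if nothing is significant. The protocol does not say so. The inference comes from H2's own wording and the lack of any other criterion. Nor does *similar* necessarily carry the 97.5% threshold over to safety.
- **Detail is left to the statistical analysis plan, which is not shown.** A margin could well be given there, and its absence from the article alone would not be a finding. But the article itself fixes a two-sided 0.05 comparison and a superiority-type analysis beside a similarity hypothesis. That mismatch is in the text at hand.
- **The tests are not insensitive throughout.** A reader might infer a general lack of power. For AE proportions, a 10-point difference would be detected more than 90% of the time at 529 per arm, so the weakness is confined to SAEs and small AE differences.

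**Conclusion.** The point holds in limited form. H2 predicts similarity, the stated safety inference is oriented to a difference, and no criterion for *comparable* is given, so a non-significant result would not support H2.

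This weighs most for SAEs. Under assumed NRT rates of 1% to 5% and the largest possible safety set, a 1.5-fold increase would be missed about 61% to 89% of the time (100% minus 39% and 11%). Even identical observed rates of 1% to 3% would not clearly exclude a doubling. For AE proportions between 30% and 70%, it applies to differences of about 5 points (power roughly 37% to 45%).

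The sizes depend on assumed event rates; the mismatch between hypothesis and analysis does not. H1, the primary effectiveness analysis and data collection are unaffected, and wording agreed before analysis settles the matter. It should be fixed, but it does not threaten the trial.

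**What to change.** Before analysis, in the statistical analysis plan:

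1. Restate H2 as estimation of the VNP minus NRT difference, and the ratio, in the proportion of participants with at least one SAE and with at least one AE.
2. Extend the 95% credible intervals planned for abstinence to these differences.
3. State that neither a non-significant result nor a posterior probability below 97.5% will be read as comparability.

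If a comparability claim is to be kept, judge it by a posterior probability of at least 97.5% that the difference lies below a justified margin. The margin must be fixed by people who have not seen safety data by arm. That rules out the Data Safety Monitoring Committee, which evaluates emerging safety data at least biannually, and the coordinating-centre staff who make the unblinded check-in calls. Members of the Clinical Advisory Committee, which also oversees safety, would qualify only if they have not seen such data.

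The cost is about one paragraph, with no extra participants or data. The downside is that the trial may be unable to claim comparable SAE safety.

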## Methods

### Design

This is a parallel two-group, superiority, open-label RCT with a 1:1 treatment allocation ratio. This study is reported using the SPIRIT reporting guidelines [22].

### Setting

The trial will be undertaken in New South Wales (NSW), Australia. Screening and consenting procedures will be completed at the Trial Coordinating Centre (TCC) at the National Drug and Alcohol Research Centre, University of New South Wales, Sydney, Australia. Baseline and follow-up computer-assisted telephone interviews (CATIs) will be completed by an independent contract research organization (CRO)—the Social Research Centre located in Melbourne, Australia.

### Participants

Participants will be people who receive a government pension or allowance (a proxy of low-SES) who smoke daily from Sydney and the wider catchment region, NSW.

#### Inclusion criteria

Participants will be included if they are at least 18 years of age; in receipt of a government pension or allowance; current daily smoker; interested in quitting smoking and willing to use the medication provided (VNP or NRT); agree to use the allocated study product and refrain from using other quit smoking medications whilst using the study products; speak English; able to provide informed consent; have a mobile telephone that can receive text messages; willing to allow the research team and study physician to access data for quality assurance and maintain integrity of trial data for the purposes of (i) the study physician to make contact if required; (ii) the CRO to conduct two CATIs; and (iii) mailing out of study products; available for follow-up over a 7-month period; and willing to complete baseline and follow-up CATIs.

#### Exclusion criteria

Exclusion criteria comprise the following: currently participating in another quit smoking programme/study; currently using any quit smoking medications or products; diagnosed with unstable angina; hospitalized for stroke, heart attack or another heart-related condition in the last 2 weeks; women who are pregnant, breastfeeding or planning to become pregnant in the next 7 months; or deemed medically unfit, by the study physician, to participate at the time of screening.

